### Exclusive education and training of staff in the INH—intervention utilizing TIME in the INH

In addition to the two-hour lecture about dementia and NPS, the staff in the INH will complete three hours of lectures, training and roleplay related to TIME. The education and training team responsible for conducting the education and training sessions consists of the project management team (a physician with special competence in nursing home medicine and two specialist registered nurses in geriatrics) and four specialist registered nurses in old age psychiatry, all of whom are familiar with TIME. The lectures will be standardized according to the steps listed in the TIME manual.

The leading ward registered nurse of each ward in the INH will attend these lectures to ensure that this leading nurse provide support to the staff during the trial. We will also encourage the nursing home physician to participate. Each staff member in the INH will be provided with the TIME manual, which describes the intervention step by step. They will also be given access to an educational film about TIME and a website to support the intervention. The three nurses who participated in the coeducation for the inclusion criteria in each unit in the INH will now hold the special responsibility for putting the model into practice based on the manual. These nurses will therefore receive three additional hours of education, training and role play related to the different components of TIME and the implementation of the intervention. In the trial, they are referred to as TIME administrators. Immediately after randomization and allocation, the project management team will contact the TIME administrators via telephone and instruct them to begin to implement the intervention according to the TIME manual for the patients included in the trial. This telephone call is made from a few days up to 1 week before the education and training sessions are given. The TIME manual is available online.

One specialist registered nurse from the education and training team will attend and supervise the TIME administrators’ first case conference on their first patient in their nursing home. For the remainder of the TIME intervention, and for the other patients included in the trial, the TIME administrators and the staff will carry out the intervention independently.

### Description of the TIME intervention

The actual assessment and treatment programme for individual patients is described in detail in the TIME manual, which provides a step-by-step guide to implementing the model. TIME consists of three overlapping phases: a registration and assessment phase; a guided reflection phase, including one or more case conferences; and an action and evaluation phase. These phases were adapted from and based on problem-solving methods in CBT [20] and are in line with reviews describing the “state of the art” for the management of NPS [4, 6]. The different components of TIME acting together thus provide an evidence-informed standardized approach to managing NPS.

In the registration and assessment phase, the nursing home physician performs an examination of the patient and the patient’s previous medical records and medications are critically reviewed. The staff gather personal background information, pain is assessed, behaviour and symptoms are registered in detailed 24-h daily records, and behaviour and symptoms are monitored with established clinical instruments, including the NPI-NH. This phase is described in detail in Table 1. The duration of this phase varies from one day up to 4 weeks, depending on the nature and burden of the symptoms. Following the registration and assessment stage, a guided reflection phase begins. In this stage, a case conference for the entire group of staff, including the physician, is conducted. Systematic reflection based on cognitive therapeutic principles is carried out. The goal of this guided reflection is to create a mutual understanding of the actual NPS of the patient and to tailor a detailed treatment plan that will be tested in the coming weeks. The case conference participants reflect on the situation using the cognitive problem-solving method, in which one problem is analysed at a time [20]. This reflection is performed systematically using a five-column sheet technique on a whiteboard, and the following five aspects are reviewed: assessed facts, interpretation, emotions, actions to take, and evaluation. The time frame and the agenda for the case conferences are outlined in Table 2. The last stage is the action and evaluation phase. In this phase, each treatment measure in the plan is put into action and is then systematically evaluated with the same assessment tools employed in the registration phase.

**Table 1 Tab1:** The registration and assessment phase

Checklist for the registration and assessment phase of TIME			
Activity	Target symptoms:		
	Agree on the primary challenges for the patient using the Neuropsychiatric Inventory-Nursing Home Version (NPI-NH) to define precise target symptoms for the assessment		
	Observation of the target symptoms using a 24-h observation form	Staff	Responsible
	NPI-NH to assess other neuropsychiatric symptoms	Staff	
	^a^Cornell Scale of Depression in Dementia (CSDD) or another scale to assess possible symptoms of depression	Staff	
	Physical assessment	Nursing home physcian	
	Review of medication	Nursing home physcian	
	^b^Mobilisation-Observation-Behaviour-Intensity-Dementia Scale (MOBID-2) to assess possible pain	Staff Nursing home physcian	
	The Clinical Dementia Rating Scale (CDR) and/or the ^c^Mini-Mental State Examination (MMSE) to assess the dementia stage	Staff Nursing home physcian	
	^d^The Physical Self-Maintenance Scale (PSMS) to assess activities in daily life	Staff	
	Collection of resident life history, including preferences and resources, using an optional questionnaire	Staff interview the resident (if possible) and/or the next of kin	
	Make an appointment, i.e., set the date, time and place for the case conference	Staff/TIME administrator	

^a^Cornell Scale of Depression in Dementia (CSDD) [26, 27]

^b^Mobilisation-Observation-Behaviour-Intensity-Dementia Scale (MOBID-2) [45]

^c^Mini-Mental State Examination (MMSE) [46]

^d^Physical Self-Maintenance Scale (PSMS) [21]

**Table 2 Tab2:** Agenda and time frame for the guided reflection meeting (case conference)

Agenda for guided reflection meeting (case conference) 1.5 h				
Activity	Preparation: Convene a meeting and prepare a meeting room with a blackboard or similar facilities (projector, if available). Check that a flip pad and markers are available	TIME administrators:		Responsible
		One is chairman for the meeting.		
		One takes notes on the whiteboard.		
		One writes the minutes on the 5-column sheet.		
	1. Status Report: Personal history and main points from the patient’s medical record are presented.	10–15 min	Decide in advance who should prepare and present the patient’s personal history and the main points from the medical record.	
	2. Create a problem list	10 min	Staff (as many as possible should attend the conference)	
	3. Prioritize problems from the list			
	4. Draw a 5−column sheet on the whiteboard: facts – interpretations (thoughts) - emotions – actions – evaluation	60 min	The leading registered nurse and the nursing home physician should attend the conference, if possible.	
	5. Describe facts from the registration and assessment phase: one problem at a time			
	6. Suggest interpretations – guided discovery – discuss and reflect on them			
	7. Describe any emotions experienced by the staff – with interpretations by the staff			
	8. Suggest ^a^SMART actions – based on the interpretations – decide how and when to perform an evaluation of the actions			
	9. Summarize interpretations and actions – close the meeting	5–10 min	TIME – administrator (chairman)	

^a^SMART (Specific-Measurable-Actual-Realistic-Time framed)

The time frame for the complete intervention with TIME will vary from 1 or 2 weeks up to 8 weeks depending on the severity and complexity of the NPS to be approached and the resources available in the nursing homes.

### Procedures for data collection

The patients’ demographic data, baseline data and primary and secondary outcomes will be collected by project nurses not affiliated with the nursing homes. All 10 assessors are nurses with substantial experience and formal training on the use of the assessment scales. They attended a one-day course on the use of the assessments scales before start of the trial. The assessments of all outcomes and covariates will be repeated at 8 and 12 weeks after baseline. The assessors will collect the data via telephone by interviewing staff members who know the patient best. The assessors will be blinded to the randomization of the nursing homes. The following data from patients’ medical records will be collected: age, gender, marital status, type of ward the patient lives in (regular somatic, special care units for dementia patients or other types), known diagnoses (chronic diseases), and dementia diagnosis.

The following data describing the nursing homes will be assessed by a questionnaire sent to the leading ward registered nurse at the start of the trial: the size of the nursing home (number of patients); the size of the unit and ward (the number of patients per unit and ward); the care factor (the number of nurses working per patient per work shift); the number of hours the nursing home physician works per patient per week in the nursing home/unit; and the number of employees per leading ward registered nurse.

Covariates that will be measured are: level of dementia, as assessed by the CDR; level of functioning in daily activities, as measured by the Physical Self-Maintenance Scale (PSMS; [21]; and physical health, as measured by the General Medical Health Rating Scale (GMHR; [22]. PSMS is a six-item scale that produces a sum score ranging from 6 to 30. A higher score denotes more severe functional impairment. GMHR is a one-item global rating scale with the categories good, fairly good, poor and very poor.

### Baseline data and primary and secondary outcome measures

A full description of the screening instruments used to assess the inclusion criteria and the primary and secondary outcomes is provided in Table 3. The primary outcome of the TIME trial is the difference in the change between intervention and control group in agitation/aggression at 8 weeks from baseline, as measured by the NPI-NH [17]. The Norwegian version of the NPI-NH has shown high inter-rater reliability and validity [23].

**Table 3 Tab3:** Primary and secondary outcome measures

What is measured (scales/tools)	Characteristics and psychometric properties of scales/tools
Primary outcome measure: The difference between the intervention group and the control group in change from baseline at 8 weeks	
Agitation/aggression (single item from the NPI-NH)	Change from baseline of agitation and aggression, as defined by the Neuropsychiatric Inventory-Nursing Home version (NPI-NH) item agitation/aggression. The NPI-NH assesses the frequency (0–4) and the severity (0–3) of 12 psychiatric and behavioural symptoms. An item score is generated by multiplying frequency and severity (0–12). A higher score indicates more frequent and severe presence of NPS.
Secondary outcome measures: The difference between the intervention group and control group in change from baseline at 8 and 12 weeks	
Neuropsychiatric symptoms (NPI-NH)	12 items described in the Neuropsychiatric Inventory Nursing Home Version (NPI-NH). Range 0–12, as described above.
Subsyndrome of agitation (NPI-NH)	The NPI-NH subsyndrome agitation is defined as the sum of the scores of the agitation/aggression, irritability, and disinhibition items. Range 0–36.
Subsyndrome affective symptoms (NPI-NH)	The NPI-NH subsyndrome affective symptoms is defined as the sum of the scores of depression and anxiety items of the NPI-NH. Range 0–24.
Subsyndrome psychotic symptoms (NPI-NH)	The NPI-NH subsyndrome psychosis is defined as the sum of the hallucinations and delusions items. Range 0–24.
Neuropsychiatric symptoms (NPI-10 NH sum score)	The NPI-10 NH sum score is the sum of the first ten items in the NPI-NH, omitting the sleep disturbances and eating disorders (primarily vegetative symptoms) items. Range 0–120.
Caregiver occupational disruptiveness (NPI-NH)	In NPI-NH, the caregiver must rate how disruptive they consider each behaviour or symptom on a five-point scale. Range 0–5. A higher score indicates a more disruptive behaviour.
Agitation (CMAI)	The Cohen-Mansfield Agitation Inventory (CMAI), which measures 29 different types of agitation and the frequency at which they occur. Range for each item 1–7. Range total score 29–203. A higher score indicates more frequent agitation. Good validity and inter-rater reliability.
Depressive symptoms (Cornell)	The Cornell Scale for Depression in Dementia, which measures the frequency of symptoms of depression.
Quality of life (QUALID)	Quality of Life in Late-stage Dementia Scale, which measures 11 behaviours rated on a 5-point Likert scale. Range 11–55. A lower score indicates higher quality of life. Good validity and inter-rater reliability
Use and dosage of psychotropic and analgesic medication (defined as daily dosage (DDD))	Psychotropic and analgesic medication given both regularly and on demand. This will be assessed using a questionnaire and extracted from patients’ records. The assessment of the medication given on demand will be obtained from patients’ records at each visit and presented as the sum in mg used for the last 21 days. These drugs will be grouped according to the Anatomical Therapeutic Chemical Index.

The secondary outcomes include the difference in the change between the two groups in agitation/aggression at 12 weeks from baseline, as measured by the NPI-NH, in the change from baseline to 8 and 12 weeks in each of the other items of the NPI-NH, the NPI-NH 10 sum score, NPI-subsyndromal agitation score (aggression/agitation + disinhibition + irritability), NPI-subsyndromal psychosis score (delusion + hallucination) and affective symptoms (depression + anxiety). These subsyndromes are based on data from a previous principal component analysis [24]. The other secondary outcomes include the difference between the two groups in the change from baseline to 8 and 12 weeks in the following measures: agitation, as measured by the Cohen-Mansfield Agitation Inventory (CMAI; [25]; symptoms of depression, as measured by the Cornell Scale for Depression in Dementia (CSDD); [26, 27]; drug use and dosage of psychotropic and analgesic medications given both regularly and on demand, coded as defined daily dosage (DDD) and grouped according to the Anatomical Therapeutic Chemical index [28]; and quality of life, as measured by the Quality of Life in Late-stage Dementia Scale (QUALID); [23, 29].

### Qualitative and quantitative methods employed in the trial to answer research questions 2 and 3

#### Focus group interviews

Focus group interviews will be conducted after the intervention is completed. Four groups of five to eight caregivers and leaders of the INH will participate. One group of nursing home leaders, one group of TIME administrators and two groups of caregivers from the staff in different nursing homes will be arranged. Because of group dynamics, the questions posed can be discussed from several points of view. These dynamics can create new perspectives and views during the discussion. We will use an interview structure based on a semi-structured interview guide that asks informants to reflect on two main themes and follows up with open and exploratory questions posed by the interviewer [30]. These two themes are 1) the feasibility of the intervention, with an emphasis on the factors that promote or inhibit the implementation of TIME, and 2) the effects that the model has on learning and staff members’ experience of coping and mastery of strain in the face of the challenging behaviour of persons with dementia. If other key themes emerge spontaneously during the interviews, time will be allotted to develop these themes. Interviews will be transcribed. A qualitative content analysis will be used to explore the findings. Systematic text condensation [31] will be performed to provide a systematic description and to develop new concepts and understandings of the phenomena. Researchers will identify units in the text and then code and reorganize these units repeatedly to emphasize the meaning content of the data.

### Questionnaire surveys administered to the staff. Methods evaluating the extent and duration of the implementation of the model by use of the RE-AIM framework

A full description of the questionnaires, including respondents and the time point(s) at which they are administered, is provided in Table 4. The implementation of TIME will be followed and assessed from the start of the study to 1 year following the study based on the RE-AIM framework [32]. RE-AIM is a widely used system for following and evaluating interventions in organizations that aim to implement new methods of practice. RE-AIM is an acronym for Reach, Efficacy, Adoption, Implementation and Maintenance. In our trial, “Reach” refers to the proportion of the staff participating in the training, routine patient assessment, and subsequent conference meetings. This information will be recorded using a registration form to assess staff participation in education and training sessions and a self-developed questionnaire administered to the staff. “Efficacy” refers to each staff member’s intervention outcomes in terms of attitudes, mastery, knowledge and skills, which we will assess and analyse using data from the focus group interviews and questionnaires. The following questionnaires will be administered for this purpose: the General Nordic Questionnaire for Psychological and Social Factors at Work regarding mastery and social interaction (QPS-Nordic) [33], the Approaches to Dementia Questionnaire (ADQ) [34], and a brief self-developed questionnaire assessing perceived competence regarding NPS. Both QPS-Nordic and ADQ are validated questionnaires used to assess these domains.

**Table 4 Tab4:** Questionnaires distributed to the staff and the leading ward registered nurse based on the RE-AIM-framework ^a^ for the evaluation of complex interventions

What is assessed	Questionnaire	Corresponding dimension of the RE-AIM framework	Time frame	Respondents in the nursing homes (NH)
Proportion of staff members participating in education and training sessions	A registration form to assess participation of staff in education and training sessions	Reach: proportion of staff in INH that actually participated in the intervention during the trial	At the start of the intervention during education sessions	All staff members in intervention nursing homes (INH)
Individual participation of staff members in effectuating the components of the model	Self-developed questionnaire	Reach: as above Maintenance: extent to which the model is sustained over time	6 and 12 months after the start of the intervention	All staff members in INH
Attitudes towards persons with dementia, mastery, social interaction, job satisfaction and self-assessment of competence with neuropsychiatric symptoms (NPS)	Approaches to the Dementia Questionnaire ^b^, QPS-Nordic ^c^ and a self-developed questionnaire for assessment of competence with NPS	Efficacy: outcomes regarding knowledge, skills and/or attitudes of the staff in NH	1 month before, and 6 and 12 months after the start of the intervention	All staff members in control nursing homes (CNH) and in INH
Clinical routines in place in NH, i.e., questions assessing daily routines of practice for assessment and treatment of NPS	Self-developed questionnaire based on evidence-informed best practice for assessment and treatment of NPS	Adoption: proportion of wards that will adopt the intervention Maintenance: extent to which the model is sustained over time	1 month before and 6 and 12 months after the start of the intervention	Leading ward registered nurse in INH and CNH
Fidelity to the main components in the model	Interview of TIME administrators by telephone using a checklist based on the components in the TIME manual	Implementation: extent to which the intervention is actually implemented	3 brief interviews, the first one 3 weeks after the start of the intervention and then at 1-month intervals	TIME administrators in INH
Organizational structure in the nursing homes: size of wards, type of unit, number of staff, etc.	Self-developed questionnaire	Implementation: possibility to assess and analyse implementation barriers and facilitators	At the start of the intervention	Leading ward registered nurse in INH and CNH

^a^RE-AIM framework: Reach-Efficacy-Adoption-Implementation-Maintenance [32]

^b^General Nordic Questionnaire for Psychological and Social Factors at Work (QPS-Nordic) [33]

^c^Approaches to Dementia Questionnaire (ADQ) [34]

In this type of intervention, “Adoption” refers to the proportion of wards and the percentage of the staff who actually adopt this method to manage NPS. We will use data from the focus group interviews and a self-developed questionnaire about participation in the routines of practice in the unit. “Implementation” refers to whether the intervention is carried out at the organization level as planned and with integrity. It will be assessed with a checklist once per month for 3 months after the start of the intervention. The checklist includes only the main components of the intervention derived from the checklist in the TIME manual. “Maintenance” refers to the degree to which the organization succeeds in maintaining the intervention after the project period. Maintenance will be measured with a self-developed questionnaire administered to units at 6 and 12 months after the intervention is implemented. This questionnaire will assess the extent to which the model and its components continue to be systematically applied. To answer the question of which factors inhibit or promote implementation, we will analyse the data from the focus group interviews and from the questionnaires.

### Data processing and statistical analysis of quantitative data

All data regarding the cluster randomized trial will be collected via telephone. The data will be registered online in the dataset prepared for the study using the data tool Checkbox via a web survey to the SQL database. The questionnaires used to collect all other data will be distributed to staff (regardless of job position) by mail and the results will be stored in the same manner as the trial data. At the 6- and 12-month assessments, questionnaires will be sent only to the staff who responded to the previous questionnaires.

The data will be presented as frequencies and percentages for categorical and means (standard deviations) for the continuous variables. The normality of continuous variables will be assessed graphically. If necessary, skewed data will be transformed. Differences in the changes in outcomes between the intervention group and the control group will be assessed by a linear mixed model with fixed effects for time component and group and the interaction between the two. A significant interaction will imply the differences in change between the groups. Random effects for patients nested within nursing homes and slopes (if significant) will be included into the model. Individual time point contrasts will be derived within each group at each time point with the corresponding 95 % confidence intervals and *p*-values. Linear mixed model correctly adjusts estimates for intra-cluster correlations as well as for intra-individual correlations due to repeated measurements in time. The model also handles unbalanced data by allowing inclusion of all available information, also from drop-outs.

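### The mailing rule for the 6- and 12-month staff questionnaires conflicts with Table 4 and leaves the staff-reported RE-AIM proportions open to selection bias

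*Protocol article*

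**What the plan says.** Two places in the protocol article define who is surveyed after the intervention.

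- *Data processing and statistical analysis of quantitative data*: for the waves at 6 and 12 months, "questionnaires will be sent only to the staff who responded to the previous questionnaires".
- Table 4, row on individual participation in carrying out the model (Reach and Maintenance): timing "6 and 12 months after the start of the intervention", respondents "All staff members in INH". This questionnaire has no earlier wave.
- Table 4, row on attitudes, mastery and competence (Efficacy): one month before and 6 and 12 months after the start, respondents "All staff members in control nursing homes (CNH) and in INH".

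The RE-AIM text says that Reach "refers to the proportion of the staff participating in the training, routine patient assessment, and subsequent conference meetings". It defines Adoption partly as a percentage of staff. It describes Maintenance at the level of the organization: "Maintenance will be measured with a self-developed questionnaire administered to units at 6 and 12 months after the intervention is implemented". Table 4 nevertheless also lists the individual-participation questionnaire as a source for Maintenance.

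Two sources stand apart from the all-staff mailing. Training attendance is captured by "A registration form to assess participation of staff in education and training sessions", and the leading ward registered nurse reports clinical routines for Adoption and Maintenance.

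**The concern.** A proportion of the staff needs the staff as its population. The mailing rule replaces that population with people who returned an earlier survey, and nothing in the article reconciles this with Table 4. Someone who works daily on a TIME ward but ignored the pre-intervention survey, or was hired after it, cannot be counted as participating or as not participating.

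Research question 3 asks whether implementation is sustainable. The Discussion says that effectiveness will be read in the light of fidelity and adoption, and that a null effect may reflect failed implementation. If returning questionnaires goes with using the model, staff-reported uptake would be distorted, and that reading with it.

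**Working it through.** **Step 1: compare the texts.** The first staff survey is one month before the start. The participation questionnaire is first sent at 6 months, so the only earlier all-staff questionnaire that can qualify someone to receive it is the pre-intervention one, which asks about other things. Table 4 says all intervention-home staff; the mailing rule says earlier responders. Both cannot hold for this row. The Efficacy row is less clear-cut: its single respondent cell covers three waves and could name the target group, with the mailing rule governing follow-up.

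**Step 2: illustrate the size.** The article gives no staff numbers or response rates, so there is no stated figure to reproduce and every input here is an assumption. Let *p* be true participation, constant over time, and let *r1* and *r0* be the response probabilities per wave of participating and other staff, independent between waves. If *k* responses related to participation are needed to appear in the data, participation among responders is

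p·r1^k / (p·r1^k + (1−p)·r0^k).

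With p = 0.5, r1 = 0.7 and r0 = 0.4, p cancels:

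- k = 1: 0.7/(0.7 + 0.4) = 0.636
- k = 2: 0.49/(0.49 + 0.16) = 0.754
- k = 3: 0.343/(0.343 + 0.064) = 0.843

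Mailing all staff means k = 1 at both waves. Under the mailing rule, k depends on two things that the article leaves open: whether response before the intervention is related to later engagement, and whether *previous* means the baseline survey only or every prior wave.

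| Pre-intervention response | *Previous* means | 6 months | 12 months |
|---|---|---|---|
| Unrelated to engagement | baseline only | 64% (k=1) | 64% (k=1) |
| Unrelated to engagement | every prior wave | 64% (k=1) | 75% (k=2) |
| Related to engagement | baseline only | 75% (k=2) | 75% (k=2) |
| Related to engagement | every prior wave | 75% (k=2) | 84% (k=3) |

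**Step 3: vary the assumed gap.**

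- 80% against 60%: k = 1, 2, 3 give 0.8/1.4 = 57%, 0.64/1.00 = 64% and 0.512/0.728 = 70%.
- Equal response: 50% for every k, so no bias.
- Reversed gap (40% for participants, 70% for others): 0.4/1.1 = 36%, 0.16/0.65 = 25% and 0.064/0.407 = 16%, a downward bias.

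**Step 4: coverage.** With a uniform 60% response, 0.6² = 36% of baseline staff answer at 6 months. At 12 months it is 0.6³ = 22% if every prior wave is required, or again 36% if only baseline is. For 50% to 80% response, 6-month coverage runs from 25% to 64%, and 12-month coverage under the stricter reading from 13% to 51%.

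**Step 5: what full mailing leaves behind.** The 64% still exceeds the true 50%, because ordinary non-response remains. Mailing everyone removes only the selection that the rule adds. This is why the number employed is needed: with it, the response rate can be reported beside the proportion.

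**The case against.** A reader might infer that Reach and Maintenance will be inflated, and increasingly so over time. The document does not support that. Step 3 shows that the direction depends on response behaviour about which the article says nothing. Growth needs both the every-prior-wave reading and responses that vary between waves; if the same people always answer, later waves select no further.

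The first survey also precedes TIME, and homes already using the model are not invited. Response to it cannot express engagement with TIME and could track it only through general disposition. If it does not, the assumed 70%/40% gap gives 64% at 6 months, the same as mailing everyone.

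Nor does the point reach all implementation data. The registration form and the leading-nurse questionnaire do not rest on the all-staff mailing, and research questions 2 and 3 also draw on case-conference records, implementation checklists and focus groups. For the Efficacy scales, following baseline responders is an ordinary closed cohort for within-person change.

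All of this stands, and it limits size and scope. It does not remove the conflict over the participation questionnaire, or the exclusion of earlier non-responders and later hires from what is meant to be a staff proportion.

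**Conclusion.** The conflict between the mailing rule and Table 4 is real, and clearest for the individual-participation questionnaire. Followed as written, the rule leaves staff-reported Reach, the staff part of Adoption so far as it uses this questionnaire, and the staff-reported contribution to Maintenance open to selection bias. Upward bias is the likelier direction if engaged staff answer more often; nil or downward bias is also possible.

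Under the assumed 70%/40% response and constant 50% participation, the rule adds 0 to 11 or 12 percentage points at 6 months (64% to 75%) and 0 to about 21 at 12 months (64% to 84%) to what mailing everyone would show. These figures illustrate sensitivity; they are not estimates for this trial. They assume a stable staff, so the exclusion of later hires comes on top and is not quantified.

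The point should be corrected, but it concerns the implementation arm of the study only. The patient outcomes are collected by telephone by blinded project nurses and are unaffected.

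**What to change.** Change the sentence in *Data processing and statistical analysis of quantitative data* to agree with Table 4:

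- At 6 and 12 months, send the participation questionnaire to all staff then employed in the intervention-home units, whatever their earlier response.
- Record the number employed in each unit at each wave as the denominator, and report the response rate with the proportion. Counting non-responders as not participating gives a floor; the proportion among responders should be labelled as such.
- Send the Efficacy questionnaires to all staff in both arms, as Table 4 says, and analyse paired change in those with a baseline questionnaire. The closed-cohort analysis is then kept as a subset.

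The cost is extra mailings and a staff count per home. Patient-level procedures do not change.
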